### Game selection and description

The games were selected based on their motor and cognitive demands. Table 1 shows the description of the games [24].

**Table 1 Tab1:** Description of the games

Game	Motor demands	Cognitive demands
Table Tilt (TT)	Multi directional and controlled center of mass displacements	Planning the motor response to achieve the goal and controlling the time to completion of the task
Rhythm Parade (RP)	Stationary marching associated with movements, with upper limb movements	Division of attention between performing lower and upper limb movements and reaching random targets with movements of one or both upper limbs
Obstacle Course (OC)	Stationary marching	Attention and planning the rapid decisions to accelerate or decelerate the march
Single Leg Extension (SLE)	Stationary control of the center of mass	Maintaining the attention and imitation of the movements of the virtual trainer
Tilty City (TC)	Lateral displacement of the center of mass associated with upper limb movements.	Planning movements to reach objects as well as division of attention between the movements of the center of mass and upper limbs
Basic Step (BS)	Ability to climb up and down steps quickly following the rhythm of the game, requiring balance control in a one-way position	Attention to the visual and auditory stimuli that guide the task
Penguim (PG)	Rapid displacements of the center of masses lateral-lateral with the feet immobile	Planning the movements in the target’s directions
Heading Soccer (HC)	Displacement of the lateral-lateral center of mass	Make a quick decision between going against or deflecting the target
Basic Rum (BR)	Fast stationary gear on the ground	Division of attention between the march and the task of memorizing objects that will be questioned at the end of the course
Torso Twist (TTW)	Stationary control of the center of mass while performing trunk rotations by moving the upper limbs, keeping the feet immobile	Maintain attention and imitate the movements of the virtual trainer

### Outcome measures

#### Feasibility, acceptability, and safety outcomes

Feasibility will be assessed by the participants’ performance in the games, measured by the score achieved. Increasing scores indicate that the participant is capable of not only playing but also improving his or her performance in the games. This is the main measure of game play that promotes motivation [24]. To determine the feasibility of the program, we will collect attendance records from each participant before and after training sessions. We will consider the exercise program to be feasible if we maintain > 50% attendance for all sessions and average > 80% attendance per session.

Acceptability will be assessed through a game satisfaction questionnaire [25]. The questionnaire consists of 18 questions, among them are participants’ perception of games (“What do you like about the games?”; “Which game do you like best?”; “Which game do you like least?”); more difficult games (“Which game did you find most difficult?”); easier games (“Which game did you find easiest?”); motivation (“Did you feel motivated to play the games?”); and discomfort during training (“Did you feel any discomfort playing the games?”).

Safety will be assessed by the proportion of participants who experienced intervention-related adverse events or any serious adverse event during the study period. An adverse event is defined as any untoward medical occurrence, such as convulsions, syncope, dizziness, vertigo, falls, or any other medical condition that requires hospitalization or leads to disability. The therapist will register the occurrence of any adverse events, and the participant’s blood pressure, oxygen pulse saturation, heart and respiratory rates, and self-perception of effort, measured by the BORG Scale [26], will be assessed before and after each training session. We will monitor the onset of any clinical conditions that could preclude the performance of physical exercises in an orthostatic position, such as cardiovascular, orthopedic, or neurological conditions.

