### Intervention

Participants will be randomly assigned to the experimental group (EG) and control group (CG), with an allocation ratio of 1:1.

Participants in the EG will participate in 14 training sessions, lasting 50 min, with a frequency of twice a week. In each training session, the participants will play five games and will be allowed three attempts at each game. The first attempt will be performed with the help of a physical therapist to correct the movements and posture of the patients through manual steering and verbal controls, while the subsequent attempts will be performed independently for the analyses of motor learning. Scores achieved in the games will be recorded. The time required to exchange the game will be approximately 2 min, and the patients will sit in a chair during this period.

Participants in the CG will be guided through verbal instructions and an illustrative booklet of guidelines carried out according to the World Health Organization, Policy Department number 385, 2014. This booklet describes physical activity, its benefits and risks, and encourages the study participants to seek health units near their residence where free physical activities are offered.

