### Adverse events

An adverse event is defined as any untoward medical occurrence in a participant which does not necessarily have a causal relationship with this intervention. Any adverse events will be reviewed by the study team, and likely causality will be assessed and reported on a form.

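### The safety endpoint counts non-serious events only if attributed to the games, and only the training therapist is named as recorder, so these events have no control-arm background rate

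*Protocol article*

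**What the plan says.** All references are to the Protocol article.

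- **Endpoint.** Under Feasibility, acceptability, and safety outcomes, safety is "the proportion of participants who experienced intervention-related adverse events or any serious adverse event during the study period". Serious events count whatever their cause; non-serious events must be related to the intervention.
- **Recorder.** The same section says "The therapist will register the occurrence of any adverse events". Next to this, vital signs and perceived effort "will be assessed before and after each training session".
- **Contact by arm.** The Intervention section says "Participants in the EG will participate in 14 training sessions, lasting 50 min, with a frequency of twice a week". For controls it says "Participants in the CG will be guided through verbal instructions and an illustrative booklet"; no therapist sessions are described for them.
- **Causality.** The Adverse events section defines an event as one "which does not necessarily have a causal relationship with this intervention". The study team then reviews each event and records its likely cause on a form.
- **Visits shared by both arms.** Under Administration of assessments, a blinded evaluator sees everyone before and after the intervention and 30 days later. No adverse-event enquiry is mentioned there. Data collection lists incidence of falls as an interview item for participants in general, without timing.
- **Use.** Hypotheses predicts that the games will cause no adverse events. The Discussion makes the main trial conditional on all feasibility criteria and hypotheses being met.

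**The concern.** The Adverse events section defines events regardless of cause, but the endpoint then applies a relatedness filter to the non-serious ones. In a two-arm trial that filter is asymmetric: a control who falls at home without serious consequence has not played the games, so the fall is excluded by rule. The same fall in the experimental group counts or not depending on how the team attributes it.

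Attribution is what the control arm could inform. Whether dizziness or falls among frail participants who train are due to training depends on how often they occur in similar participants who do not train. The randomised controls are the trial's only internal source for that, and the endpoint does not use them for non-serious events.

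The endpoint's window is also wider than the stated observation. It covers the study period, while the named recorder's described contact is the training. At stake is a go/no-go decision: a favourable safety result could reflect how events were attributed, or that few were sought outside sessions.

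**Working it through.** **1. The plan's only sample-size figure.** From Sample size: 12 evaluable per group and 20% dropout. 12 / (1 − 0.20) = 15 per group, 30 in total. This reproduces the stated target. No adverse-event rate or safety threshold is given, so the safety outcome has no figure of its own to reproduce.

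**2. What can enter the endpoint, following the text.**

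| Event | Experimental group | Control group |
|---|---|---|
| Serious, any cause | counts | counts |
| Non-serious, judged related | counts | cannot arise from the games |
| Non-serious, judged unrelated | does not count | does not count |

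If the booklet were itself read as an intervention, only control events put down to it would count. Background events would still be excluded.

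**3. Stated observation against the stated window.** 14 sessions at two a week take 14 / 2 = 7 weeks, or 49 days. Adding the 30 days to follow-up gives 49 + 30 = 79 days. The share without training contact is 30 / 79 = 38% in the experimental group and 100% in controls. (Table 2 numbers the intervention as days 3 to 16, which cannot be calendar days at two sessions a week, so I use the 7 weeks.)

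**4. Information the rule leaves out.** The documents give no background risk, so assume a true risk p of at least one non-serious event, equal in both arms. Expected controls affected = 15 × p:

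- p = 0.10: 1.5
- p = 0.20: 3.0
- p = 0.30: 4.5
- p = 0.40: 6.0

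The number counted is 0 in every case.

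**5. Weight of one judgement.** One participant is 1 / 15 = 6.7 percentage points of an arm, or 1 / 12 = 8.3 points with 12 evaluable. Since the hypothesis is that no events are caused, one attribution can decide it.

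**6. What zero events would show.** The exact two-sided 95% upper limit is 1 − 0.025^(1/n). For n = 15 it is 21.8%; for n = 12 it is 26.5%. This reading of the experimental group needs no control data for events during sessions.

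**7. Illustration only: unequal capture if all-cause events were set side by side.** Assume a true risk of 20% in both arms, 90% capture in the experimental group and 25% to 50% in controls. Observed rates would be 0.20 × 0.90 = 18% against 0.20 × 0.25 = 5% to 0.20 × 0.50 = 10%. The spurious excess is 18 − 10 = 8 to 18 − 5 = 13 points, or 2.7 against 0.75 to 1.5 participants out of 15. All three rates are assumptions, and the plan does not specify this comparison.

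**The case against.** The case for the plan has real force.

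- **No between-arm safety comparison is specified.** Statistical analyses presents feasibility outcomes descriptively and does no hypothesis testing. A reader might infer that the safety result as a whole cannot be interpreted by arm. The documents do not support that: serious events count in both arms, and events during sessions can be read within the experimental group. What stands is narrower: non-serious events, and events outside sessions.
- **A condensed article may leave event elicitation to the full protocol.** This is fair. The text does not say that the therapist is the only recorder, and the before-and-after timing attaches to the vital signs and effort rating. Missing procedural detail alone would not be a point. But the endpoint rule is stated, and it excludes non-serious control events however well they are collected.
- **Controls are seen, and falls are listed.** Both arms attend the same blinded assessments. It would be wrong to say that controls have no study contact or that the control arm is lost. However, the falls item has no timing, is not tied to the safety endpoint, and does not cover dizziness, vertigo or syncope.
- **The Blinding section says all outcomes are assessed blind.** It does not mention the causality review, and the therapist who registers events delivers the training.
- **The two definitions of an adverse event might be read as contradictory.** Both rest on any untoward medical occurrence, and the safety section adds examples after the words such as. Recording broadly and then reporting a subset is coherent, so I make no point of this.

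**Conclusion.** The concern holds in a limited form. As written, the endpoint excludes non-serious events in controls. No stated route captures such events in controls, or in either arm between the last session and the 30-day visit, although the endpoint covers the whole study period. For non-serious events, the hypothesis that the games are harmless then rests on the study team's attribution, without stated blinding and without a control rate to set it against.

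The exclusion needs no assumption beyond reading the intervention as the games. The 6.7-point step and the 21.8% upper limit assume 15 per arm. The background risks and the 8 to 13 point excess are illustrations, not estimates of bias in this trial. No sample-size figure changes. This should be corrected because the result feeds the decision on the main trial; it does not invalidate the trial.

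**What to change.** 1. At the existing post and 30-day assessments, ask both arms one identical structured question on adverse events and falls since the last assessment. Ask it last. Tie the falls item under Data collection to these two visits.
2. Make the safety outcome the proportion with any adverse event, any fall and any serious event, by arm and regardless of causality, each with an exact 95% confidence interval.
3. Report intervention-related events as a secondary outcome.
4. Report events the therapist observes during sessions separately, as a description of the experimental group only and not as a between-arm contrast.

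The cost is one question at two visits that already exist, plus an amendment to the wording. Event counts will be somewhat higher. Answers may hint at allocation, which is why the question comes last; a small risk of unblinding the assessor remains. Recruitment stood at about half when the article was written, so participants already past a visit may lack the item. Give the number asked as the denominator for each arm and visit.

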#### Clinical outcomes

Clinical outcomes will be the following: (1) postural control, assessed by the Mini-Balance Evaluation Systems Test (Mini-BEST-Test) [27]; (2) gait, assessed by the Functional Gait Assessment (FGA) [28]; (3) cognition, assessed by the Montreal Cognitive Scale (MoCA) [29]; (4) quality of life, assessed by the Brazilian version of the Short Form 36 (SF-36) [30]; (5) mood, assessed by the Geriatric Depression Scale (GDS-15) [31]; and (6) fear of falling, assessed by the Falls Efficacy Scale (FES-I) [32].

Due to the absence of specific studies on minimal detectable change (MDC) in frailty, we will consider a change of 3.5 points in the Mini-BEST-Test [33] and 4.2 points in the FGA [34] as significant. The MDC of the other scales has not yet been established.

### Participant timeline

Table 2 illustrates the process of enrolling participants in the study, the intervention, and timing of assessments.

**Table 2 Tab2:** Schedule of enrolment, interventions, and assessments

	Study period				
Timepoint	Day 1	Day 2	Days 3 to 16	Day 17	Day 47
Enrollment	X				
Eligibility screen	X				
Informed consent	X				
Allocation	X				
Interventions			X		
Assessments		X		X	X
Initial assessment (pre)		X			
Final assessment (post)				X	
Follow-up assessment					X

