### Administration of assessments

The same-trained researcher will provide the patient with a free informed consent form, which also contains information on the possible benefits that the interventions may bring and possible risks and indemnities to patients, also emphasizing that the patient can withdraw from the research at any time without any contradictions. On the same day, the evaluator will clarify all doubts regarding the research project and inform the volunteers that all data resulting from the survey will be used for scientific purposes. The same-trained researcher, blinded to treatment allocation, will evaluate all participants at three timepoints: immediately pre and post interventions and 30 days after the end of the interventions (follow-up). Participants will be asked not to inform the evaluators about the kind of intervention they have received.

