### Blinding

Blinding of trial participants and the intervention facilitator is not possible. All outcomes will be assessed by a researcher blinded to group allocation. Participants will be asked not to disclose their allocation to the physical therapist who will participate in the assessments.

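### Table 2 schedules allocation before the baseline assessment, and nothing withholds the arm, so unblinded participants may know their group when baseline is measured

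*Protocol article*

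**What the plan says.** Of Table 2, the Participant timeline section says: "Table 2 illustrates the process of enrolling participants in the study, the intervention, and timing of assessments". On Day 1 the table marks enrolment, the eligibility screen, consent and allocation. On Day 2 it marks the row "Initial assessment (pre". The sessions follow on Days 3 to 16, the final assessment on Day 17 and the follow-up on Day 47.

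The Administration of assessments section times the assessments as "immediately pre and post interventions and 30 days after the end of the interventions (follow-up". The first assessment is thus tied to the start of the intervention, not to randomisation.

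On who knows the arm, the Blinding section states: "Blinding of trial participants and the intervention facilitator is not possible". It adds: "All outcomes will be assessed by a researcher blinded to group allocation". Participants are asked to keep their arm from the assessor: "Participants will be asked not to disclose their allocation to the physical therapist who will participate in the assessments". Administration of assessments makes a similar request: "Participants will be asked not to inform the evaluators about the kind of intervention they have received".

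**The concern.** A baseline is free of the effect of assignment only if it is taken before the participant knows the assignment. Here the contrast is supervised game sessions against verbal advice and a booklet. Disappointment or enthusiasm on learning the arm is plausible, and could alter answers on quality of life, mood and fear of falling, or effort on a performance test. A blinded assessor protects the scoring but does not remove what the participant knows.

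The baseline matters because the plan looks at change. Clinical outcomes sets change thresholds of 3.5 points (Mini-BEST-Test) and 4.2 points (FGA). Statistical analyses uses effect sizes to judge whether change over time can be detected and to pick the most suitable primary outcome for the later trial. In addition, anyone who leaves between allocation and the initial assessment stays in the intention-to-treat population with no baseline at all.

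**Working it through.** **1. Order of steps.** Read row by row, Table 2 gives allocation in the first time column, initial assessment in the second and interventions in the third. The general assessments row also has its first mark in the second column. Two rows agree, so the order is not a column displaced in text extraction.

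**2. Meaning of the day labels.** Fourteen sessions at two a week take 14/2 = 7 weeks, yet Days 3 to 16 are 16 − 3 + 1 = 14 labels. These look like session numbers. Day 47 = 17 + 30 uses calendar days. The real gap between allocation and baseline is therefore unknown, but the order is unaffected.

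**3. Knowledge of the arm.** Participants are not blinded. No section delays disclosure until baseline is done, and none gives the day of disclosure. The schedule thus permits knowledge of the arm at baseline but does not establish it.

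**4. Which measures.** SF-36, GDS-15 and FES-I ("fear of falling, assessed by the Falls Efficacy Scale (FES-I") are reported by the participant. Mini-BEST-Test, FGA and MoCA are scored by a blinded assessor, so only the participant's effort could shift.

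**5. Size, under assumptions.** Let *b* be the between-arm shift at baseline, in SD units, caused by knowing the arm and taken as confined to baseline. Let *r* be the correlation between baseline and post values, with equal SDs. The documents give neither; I take *b* = 0.1 to 0.5 and *r* = 0.5 to 0.7.

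- Difference in change from baseline: bias = −*b*, so 0.1 to 0.5 SD in size.
- Baseline-adjusted difference (not specified in the article; for comparison only): bias = −*r* × *b*, so 0.5 × 0.1 = 0.05 to 0.7 × 0.5 = 0.35 SD in size.
- Difference in post values alone: bias by this route = 0.

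**6. Loss before baseline.** The plan's own figure first: 12/(1 − 0.20) = 15 per group, 30 in total, which agrees with the Sample size section. One participant lost between allocation and baseline is 1/15 = 6.7% of an arm.

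**7. Is the order needed?** Randomisation stratifies only on pre-frail against frail. That comes from Fried's criteria, which are an inclusion criterion and so known at screening. Nothing else from allocation is needed for the assessment, and nothing from the assessment is needed for allocation.

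**The case against.** Four points can be made in the plan's favour.

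- **Allocation is not disclosure.** A reader might infer that participants do give their baseline knowing their arm. The article does not say so. One of the two non-disclosure requests concerns an intervention already received, which fits the later visits better, and the other is undated. This stands: the schedule permits the problem but does not prove it.
- **The planned contrast may be untouched.** A reader might infer that all between-group results are biased. Statistical analyses specifies an unadjusted mean difference and does not say that it is computed on change. If it is taken on post values, this route does not bias it. This stands too, but the change thresholds and the change-over-time effect sizes remain exposed.
- **The bias is small against the planned precision.** The 95% half-width for a mean difference is about 2.05 × √(2/15) = 0.75 SD with 15 per arm and 2.07 × √(2/12) = 0.85 SD with 12. A shift at the low end of the assumed range would be hard to see. That limits the harm, but an avoidable bias is not excused by a wide interval.
- **Feasibility results do not depend on it.** Game scores, attendance, satisfaction and adverse events do not use the initial clinical assessment, and no hypothesis is tested. This stands and lowers the severity.

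A reader might also put the loss at 1/12 = 8.3% of an arm. Twelve is the target number with full data; 15 are randomised per arm, so 6.7% is the right share, and one loss lies within the dropout allowance of 15 − 12 = 3 per arm.

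**Conclusion.** The point holds at moderate severity. As published, allocation precedes the baseline assessment in an open trial, with nothing to keep the arm from participants in between. Self-reported baselines can be distorted, and effort on the performance tests possibly so. A distortion would pass in full into change-score differences: 0.1 to 0.5 SD under the assumed shift, which rests on no figure in the documents and on the shift being confined to baseline. What is at risk is the change-based effect sizes and, through them, the choice of a later primary outcome. The documents do not support saying that participants certainly knew their arm, that all six clinical outcomes are biased, or that the main feasibility conclusions are undermined.

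**What to change.** For participants still to be enrolled, move allocation in Table 2 to after the initial assessment and before the first session. Screening already supplies the stratum, so no visit or staff is added.

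If disclosure is in fact already held back until baseline is complete, state this in the Blinding section and in Table 2. That would remove the bias from knowing the arm, though a participant lost between the two steps would still lack a baseline.

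The cost is a short protocol amendment and a sample that mixes two orders, since Trial status puts recruitment at about 50%. Report how many participants in each arm were enrolled under the present order. A sensitivity analysis by order would tell little: about 0.5 × 30 = 15 participants in each subset, or 7 to 8 per arm.
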